#### Analysis of secondary outcomes

For the NRS score, comparisons among the three groups will be assessed by a mixed-effect model with repeated measurement (MMRM) analysis using the NRS score at all follow-up time points as the dependent variable, treatment as the main factor, and the baseline value as a covariate. We set the model as

*y*_*ij*_ = *α* + *u*_*i*_ + *β*_1_time_*ij*_ + *β*_2_treat_*i*_ + *ε*_*ij*_

where *α* is the overall average and *u*_*i*_ is an unknown random effect represented as a subject-specified effect. *β*_1_ and *β*_2_ are unknown fixed effects represented as time and treatment effects, respectively. The covariance matrix *G* is unstructured, and *u*_*i*_~*N*(0, *G*). The random error *ε*_*ij*_~*N*(0, *R*_*i*_). The MMRM for secondary outcomes will be handled by PROC MIXED (SAS). The estimators of unknown parameters will be calculated using an expectation maximalization algorithm, which we expect will converge for the 480 participants in three groups and a single random intercept. If non-convergence does happen, we will consider correcting the initial value, changing the random effect, or using another analysis method like generalized estimating equations. Also, we will test the estimators or models based on a likelihood test and Bayesian information criterion methods.

The modified MMRM also has the center effect and time × treatment effect and it will be used in the sensitivity analysis. The modified MMRM is as follows:$$ {y}_{ij}=\upalpha +{u}_i+{\upbeta}_1{\mathrm{time}}_{ij}+{\upbeta}_2{\mathrm{treat}}_i+{\upbeta}_3{\mathrm{time}}_{ij}\times {\mathrm{treat}}_i+{\upbeta}_4{\mathrm{center}}_i+{\upvarepsilon}_{ij} $$

where α, u_*i*_, β_1_, β_2_, and ε_*ij*_ are defined as above. β_3_ and β_4_ are unknown fixed effects.

The same approach will be used to analyze the pain, function, and stiffness WOMAC subscales, and SF-12. If normality is violated in the continuous variables, a transformation will be performed before the comparison. A chi-square test will be used for the patient global assessment. These outcomes are shown in Table 2.

**Table 2 Tab2:** Primary and secondary outcomes

Outcomes	EA (*n*)	MA (*n*)	SAb (*n*)	*P* value	Pairwise comparison					
					EA vs. SA		MA vs. SA		EA vs. MA	
					Difference (95% CI)	*P* value	Difference (95% CI)	*P* value	Difference (95% CI)	*P* value
Success rate, no. (%)										
4 weeks	x (xx.x)	x (xx.x)	x (xx.x)	–	xx.x (xx.x- xx.x)	xx.x	xx.x (xx.x- xx.x)	xx.x	–	–
8 weeks	x (xx.x)	x (xx.x)	x (xx.x)	–	xx.x (xx.x- xx.x)	xx.x	xx.x (xx.x- xx.x)	xx.x	–	–
16 weeks	x (xx.x)	x (xx.x)	x (xx.x)	–	xx.x (xx.x- xx.x)	xx.x	xx.x (xx.x- xx.x)	xx.x	–	–
26 weeks	x (xx.x)	x (xx.x)	x (xx.x)	–	xx.x (xx.x- xx.x)	xx.x	xx.x (xx.x- xx.x)	xx.x	–	–
Numerical Rating Scale, mean (SD)										
Baseline	xx.x (xx.x)	xx.x (xx.x)	xx.x (xx.x)	xx.x	xx.x (xx.x- xx.x)	xx.x	xx.x (xx.x- xx.x)	xx.x	xx.x (xx.x- xx.x)	xx.x
4 weeks	xx.x (xx.x)	xx.x (xx.x)	xx.x (xx.x)		xx.x (xx.x- xx.x)		xx.x (xx.x- xx.x)		xx.x (xx.x- xx.x)	
8 weeks	xx.x (xx.x)	xx.x (xx.x)	xx.x (xx.x)		xx.x (xx.x- xx.x)		xx.x (xx.x- xx.x)		xx.x (xx.x- xx.x)	
16 weeks	xx.x (xx.x)	xx.x (xx.x)	xx.x (xx.x)		xx.x (xx.x- xx.x)		xx.x (xx.x- xx.x)		xx.x (xx.x- xx.x)	
26 weeks	xx.x (xx.x)	xx.x (xx.x)	xx.x (xx.x)		xx.x (xx.x- xx.x)		xx.x (xx.x- xx.x)		xx.x (xx.x- xx.x)	
WOMAC pain subscale, mean (SD)										
Baseline	xx.x (xx.x)	xx.x (xx.x)	xx.x (xx.x)	xx.x	xx.x (xx.x- xx.x)	xx.x	xx.x (xx.x- xx.x)	xx.x	xx.x (xx.x- xx.x)	xx.x
4 weeks	xx.x (xx.x)	xx.x (xx.x)	xx.x (xx.x)		xx.x (xx.x- xx.x)		xx.x (xx.x- xx.x)		xx.x (xx.x- xx.x)	
8 weeks	xx.x (xx.x)	xx.x (xx.x)	xx.x (xx.x)		xx.x (xx.x- xx.x)		xx.x (xx.x- xx.x)		xx.x (xx.x- xx.x)	
16 weeks	xx.x (xx.x)	xx.x (xx.x)	xx.x (xx.x)		xx.x (xx.x- xx.x)		xx.x (xx.x- xx.x)		xx.x (xx.x- xx.x)	
26 weeks	xx.x (xx.x)	xx.x (xx.x)	xx.x (xx.x)		xx.x (xx.x- xx.x)		xx.x (xx.x- xx.x)		xx.x (xx.x- xx.x)	
WOMAC function subscale, mean (SD)										
Baseline	xx.x (xx.x)	xx.x (xx.x)	xx.x (xx.x)	xx.x	xx.x (xx.x- xx.x)	xx.x	xx.x (xx.x- xx.x)	xx.x	xx.x (xx.x- xx.x)	xx.x
4 weeks	xx.x (xx.x)	xx.x (xx.x)	xx.x (xx.x)		xx.x (xx.x- xx.x)		xx.x (xx.x- xx.x)		xx.x (xx.x- xx.x)	
8 weeks	xx.x (xx.x)	xx.x (xx.x)	xx.x (xx.x)		xx.x (xx.x- xx.x)		xx.x (xx.x- xx.x)		xx.x (xx.x- xx.x)	
16 weeks	xx.x (xx.x)	xx.x (xx.x)	xx.x (xx.x)		xx.x (xx.x- xx.x)		xx.x (xx.x- xx.x)		xx.x (xx.x- xx.x)	
26 weeks	xx.x (xx.x)	xx.x (xx.x)	xx.x (xx.x)		xx.x (xx.x- xx.x)		xx.x (xx.x- xx.x)		xx.x (xx.x- xx.x)	
WOMAC stiffness subscale, mean (SD)										
Baseline	xx.x (xx.x)	xx.x (xx.x)	xx.x (xx.x)	xx.x	xx.x (xx.x- xx.x)	xx.x	xx.x (xx.x- xx.x)	xx.x	xx.x (xx.x- xx.x)	xx.x
4 weeks	xx.x (xx.x)	xx.x (xx.x)	xx.x (xx.x)		xx.x (xx.x- xx.x)		xx.x (xx.x- xx.x)		xx.x (xx.x- xx.x)	
8 weeks	xx.x (xx.x)	xx.x (xx.x)	xx.x (xx.x)		xx.x (xx.x- xx.x)		xx.x (xx.x- xx.x)		xx.x (xx.x- xx.x)	
16 weeks	xx.x (xx.x)	xx.x (xx.x)	xx.x (xx.x)		xx.x (xx.x- xx.x)		xx.x (xx.x- xx.x)		xx.x (xx.x- xx.x)	
26 weeks	xx.x (xx.x)	xx.x (xx.x)	xx.x (xx.x)		xx.x (xx.x- xx.x)		xx.x (xx.x- xx.x)		xx.x (xx.x- xx.x)	
Patient global assessment, mean (SD)										
Baseline	xx.x (xx.x)	xx.x (xx.x)	xx.x (xx.x)	xx.x	xx.x (xx.x- xx.x)	xx.x	xx.x (xx.x- xx.x)	xx.x	xx.x (xx.x- xx.x)	xx.x
4 weeks	xx.x (xx.x)	xx.x (xx.x)	xx.x (xx.x)		xx.x (xx.x- xx.x)		xx.x (xx.x- xx.x)		xx.x (xx.x- xx.x)	
8 weeks	xx.x (xx.x)	xx.x (xx.x)	xx.x (xx.x)		xx.x (xx.x- xx.x)		xx.x (xx.x- xx.x)		xx.x (xx.x- xx.x)	
16 weeks	xx.x (xx.x)	xx.x (xx.x)	xx.x (xx.x)		xx.x (xx.x- xx.x)		xx.x (xx.x- xx.x)		xx.x (xx.x- xx.x)	
26 weeks	xx.x (xx.x)	xx.x (xx.x)	xx.x (xx.x)		xx.x (xx.x- xx.x)		xx.x (xx.x- xx.x)		xx.x (xx.x- xx.x)	
SF-12 physical health, mean (SD)										
Baseline	xx.x (xx.x)	xx.x (xx.x)	xx.x (xx.x)	xx.x	xx.x (xx.x- xx.x)	xx.x	xx.x (xx.x- xx.x)	xx.x	xx.x (xx.x- xx.x)	xx.x
4 weeks	xx.x (xx.x)	xx.x (xx.x)	xx.x (xx.x)		xx.x (xx.x- xx.x)		xx.x (xx.x- xx.x)		xx.x (xx.x- xx.x)	
8 weeks	xx.x (xx.x)	xx.x (xx.x)	xx.x (xx.x)		xx.x (xx.x- xx.x)		xx.x (xx.x- xx.x)		xx.x (xx.x- xx.x)	
16 weeks	xx.x (xx.x)	xx.x (xx.x)	xx.x (xx.x)		xx.x (xx.x- xx.x)		xx.x (xx.x- xx.x)		xx.x (xx.x- xx.x)	
26 weeks	xx.x (xx.x)	xx.x (xx.x)	xx.x (xx.x)		xx.x (xx.x- xx.x)		xx.x (xx.x- xx.x)		xx.x (xx.x- xx.x)	
SF-12 mental health, mean (SD)										
Baseline	xx.x (xx.x)	xx.x (xx.x)	xx.x (xx.x)	xx.x	xx.x (xx.x- xx.x)	xx.x	xx.x (xx.x- xx.x)	xx.x	xx.x (xx.x- xx.x)	xx.x
4 weeks	xx.x (xx.x)	xx.x (xx.x)	xx.x (xx.x)		xx.x (xx.x- xx.x)		xx.x (xx.x- xx.x)		xx.x (xx.x- xx.x)	
8 weeks	xx.x (xx.x)	xx.x (xx.x)	xx.x (xx.x)		xx.x (xx.x- xx.x)		xx.x (xx.x- xx.x)		xx.x (xx.x- xx.x)	
16 weeks	xx.x (xx.x)	xx.x (xx.x)	xx.x (xx.x)		xx.x (xx.x- xx.x)		xx.x (xx.x- xx.x)		xx.x (xx.x- xx.x)	
26 weeks	xx.x (xx.x)	xx.x (xx.x)	xx.x (xx.x)		xx.x (xx.x- xx.x)		xx.x (xx.x- xx.x)		xx.x (xx.x- xx.x)	

*EA* electro-acupuncture, *MA* manual acupuncture, *SA* sham acupuncture, *WOMAC* Western Ontario and McMaster Universities Osteoarthritis Index, *SD* standard deviation, *SF-12* 12-item Short Form Health Survey

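### The unstructured label is put on a single random-intercept variance, where it does nothing, and the covariance of the four visits is given no structure

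*SAP article*

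**What the plan says.** In the SAP article, Analysis of secondary outcomes, the NRS score at all follow-up visits is modelled with a subject effect u_i, time and treatment. The subject effect is normal with covariance G, and "The covariance matrix *G* is unstructured". The errors are normal with covariance R_i, and nothing is said about the form of R_i. The fit is by an iterative algorithm "which we expect will converge for the 480 participants in three groups and a single random intercept". The same approach applies to the three WOMAC subscales and the two SF-12 scores.

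A second model adds further terms: "The modified MMRM also has the center effect and time × treatment effect and it will be used in the sensitivity analysis". Its subject effect and error term are defined as in the first model.

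If the fit fails, "we will consider correcting the initial value, changing the random effect, or using another analysis method like generalized estimating equations". The article adds that "we will test the estimators or models based on a likelihood test and Bayesian information criterion methods", without naming candidate covariance structures. Table 2 has a cell for a difference with 95% CI at each visit for each continuous score.

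**The concern.** In an MMRM the covariance among a patient's visits is normally left unstructured, so that each visit has its own variance and each pair its own correlation. The article uses the right word but attaches it to a matrix that has only one element here. The matrix that carries the visit-to-visit covariance is R_i, and it is left open. This is more than a detail left out of a condensed article: a covariance structure is stated, and it is stated for the wrong matrix.

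The design makes it unwise to impose constant variance and correlation by accident. Weeks 4 and 8 fall within the 8-week treatment period (week 8 at its end), weeks 16 and 26 come after it, and the gaps between visits are 4, 8 and 10 weeks. At stake is the calibration of the week-specific intervals, including those on whether an effect lasts after treatment.

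**Working it through.** **Inputs from the article.** Four follow-up visits (weeks 4, 8, 16, 26); one random intercept; PROC MIXED; 480 patients in three arms, so 480/3 = 160 per arm, which agrees with the sample size section: 128/(1 − 0.20) = 160. The article gives no figure for the covariance or for SDs by visit, so there is nothing to reproduce on that point and the SDs below are assumptions.

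**Step 1: what the stated structure does.** With one random intercept, G is 1 × 1. Any structure on a 1 × 1 matrix is one variance parameter.

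**Step 2: reading (a), R_i = σ²I.** This is what PROC MIXED fits if no residual structure is requested. Then Var(y_ij) = G + σ² at every visit and the correlation of any two visits is G/(G + σ²). That is compound symmetry, with two parameters.

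**Step 3: reading (b), R_i unstructured.** A 4 × 4 covariance has 4 × 5/2 = 10 distinct elements. Adding G gives 11 parameters for 10 quantities, so the intercept variance is redundant and cannot be separated from R_i.

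**Step 4: consequence of reading (a) for week-specific differences.** Take complete data and the model with time × treatment. The estimate at visit t is then the difference in means at that visit, but its SE uses the variance averaged over visits, v̄ = mean of SD_t². Coverage of a nominal 95% interval is

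coverage_t = 2Φ(1.96 × √v̄ / SD_t) − 1.

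Example with residual SDs 1.6/1.8/2.2/2.5: v̄ = (2.56 + 3.24 + 4.84 + 6.25)/4 = 4.2225 and √v̄ = 2.055. With 160 per arm the model SE is 2.055 × √(2/160) = 0.230 at every visit. The true values are 0.179, 0.201, 0.246 and 0.280. At week 26, 1.96 × 2.055/2.5 = 1.611, which gives 89.3%.

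| Assumed SDs, weeks 4/8/16/26 | √v̄ | Coverage, weeks 4/8/16/26 (%) |
|---|---|---|
| 2.0/2.0/2.0/2.0 | 2.000 | 95.0/95.0/95.0/95.0 |
| 1.9/2.0/2.1/2.2 | 2.053 | 96.6/95.6/94.5/93.3 |
| 1.6/1.8/2.2/2.5 | 2.055 | 98.8/97.5/93.3/89.3 |
| 2.5/2.2/1.8/1.6 | 2.055 | 89.3/93.3/97.5/98.8 |

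**Step 5: check by simulation.** With two arms of 128, complete data, SDs 1.8/2.0/2.2/2.4, correlation 0.7 between adjacent visits decaying as AR(1), and 20,000 replicates, coverage was 97.8/96.3/94.0/91.5%. The formula gives 97.9/96.2/94.0/91.5%.

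**Step 6: the averaged effect.** In the same simulations (this scenario, equal SDs of 2, and SDs 1.5/2.0/2.5/3.0), the treatment effect averaged over visits kept 94.6–95.0% coverage. With complete data, the main model's single treatment effect is therefore not harmed.

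**The case against.** Several points on the other side stand.

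- A reader might infer that the plan forces equal variance and equal correlation. It does not say so: R_i is written as a general matrix, and compound symmetry follows only from the software default.
- A reader might infer that neither reading can give unstructured-MMRM inference. Under reading (b) the total covariance G·J + R_i (J the matrix of ones) is still identified and can be any valid 4 × 4 covariance matrix. If the fit completes, estimates and SEs are those of an unstructured model. Failure to converge is possible but not certain.
- A reader might infer that the intervals in Table 2 are wrong, and too narrow at week 26. Without visit SDs neither can be concluded. Equal SDs give no error with complete data, and falling SDs reverse the direction. Unequal correlations alone do not change week-specific coverage when data are complete.
- Table 2 does not say which model fills its cells. The main model has no time × treatment term and yields one common difference, so week-specific model estimates could come only from the modified model, a sensitivity analysis. That mismatch is a separate matter.
- Drop-out adds little bias. In an 800-run simulation with 160 per arm, rising SDs and about 15% score-dependent drop-out, bias in the EA–SA difference was at most about 0.02 points.

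The provision for likelihood and BIC checks does not settle the point, because no candidate structures are listed. The fallbacks have no fixed order and apply only on non-convergence, and a compound-symmetry fit would normally converge. An article may leave detail to the full SAP, but that does not explain a label attached to the wrong matrix.

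**Conclusion.** The point holds as a specification error: the only covariance structure that the plan states has no effect, and the matrix that matters has none. The text needs correcting under either reading of R_i.

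The size is conditional. It assumes that R_i takes the software default, that week-specific intervals come from the interaction model, that data are complete, and that visit SDs are as assumed. Then coverage runs from nominal (equal SDs) to between 89.3% and 98.8% for SDs that rise, or fall, between 1.6 and 2.5. The harm is confined to week-specific differences in continuous secondary outcomes, which the article treats as supportive. The primary Z-test does not use this model. The correction is worth making before analysis but does not threaten the trial's main conclusion.

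**What to change.** Remove u_i and state that R_i is an unstructured 4 × 4 covariance over weeks 4, 8, 16 and 26. In PROC MIXED: visit as a class variable and REPEATED visit / SUBJECT=patient TYPE=UN, with no RANDOM statement. Apply this to both the main and the modified model, and reword the sentence so that unstructured refers to R_i and not G. Replace the open list of remedies for non-convergence with a fixed order of simpler structures for R_i, for example heterogeneous Toeplitz and then heterogeneous compound symmetry. Say which model supplies the week-specific cells of Table 2.

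The cost is a few sentences and one line of code. The model estimates ten covariance parameters in place of two, which 480 patients with four visits support easily. The article says that it was written before data collection ended, so the change can still be fixed in advance if it is made before the data are seen.

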### Objectives

The objective of the current study is to determine if EA or MA improve clinical outcomes at 8 weeks in patients with KOA. The following two null hypotheses will be tested:H1: There is no difference in the patients’ response rate between the EA group and the SA group.H2: There is no difference in the patients’ response rate between the MA group and the SA group.

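### The main repeated-measures model for the supportive continuous outcomes has no time × treatment term, so it cannot supply Table 2's week-by-week differences; separately, both printed equations leave out the stated baseline covariate

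*SAP article*

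**What the plan says.** All of this is in the SAP article.

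- **Main model (Analysis of secondary outcomes).** The words describe a repeated-measures model of the NRS score at all follow-up visits, with "treatment as the main factor, and the baseline value as a covariate". The equation printed beneath has five terms: intercept α, subject effect u_i, β1·time, β2·treat and error ε_ij. The two coefficients "are unknown fixed effects represented as time and treatment effects, respectively". It has no baseline term and no interaction.
- **Second model (same section).** "The modified MMRM also has the center effect and time × treatment effect and it will be used in the sensitivity analysis". Its equation adds β3·time × treat and β4·center. It also has no baseline term.
- **Scope.** "The same approach will be used to analyze the pain, function, and stiffness WOMAC subscales, and SF-12". The section then says "These outcomes are shown in Table 2".
- **Table 2.** The block for each of these outcomes (for example "Numerical Rating Scale, mean (SD)") has rows for baseline and weeks 4, 8, 16 and 26. Each row has its own difference (95% CI) cell for EA vs. SA, MA vs. SA and EA vs. MA. There is only one P value per pair for the whole block.
- **Objectives and primary analysis.** The aim is to see whether EA or MA "improve clinical outcomes at 8 weeks in patients with KOA". The two hypotheses that follow concern response rate, and Analysis of the primary outcome tests them at 8 weeks with a Z-test. General analysis principles gives the secondary outcomes a supporting role.

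**The concern.** The table and the main model answer different questions. Table 2 asks for four follow-up differences per pair, and the main model has one parameter per pair. The weekly cells must therefore come from somewhere else, either the sensitivity model or the raw means, and the plan does not say which. The P value next to them would come from the main model and test the average over follow-up. A reader would naturally take it as the test of the differences printed beside it.

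The average is also a particular mixture here. Treatment ends at week 8, so two of the four visits (weeks 16 and 26) fall 8 and 18 weeks after the last session. If the secondary outcomes are to support an 8-week primary result, the 8-week difference is the natural quantity to show. The main model does not isolate it.

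The baseline mismatch is a separate matter. An analyst coding from the words adjusts for baseline, and one coding from either equation does not.

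**Working it through.** **1. What the main model can estimate.** Under y_ij = α + u_i + β1·time_ij + β2·treat_i + ε_ij, the EA minus SA difference at any week j is

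E[y | EA, j] − E[y | SA, j] = β2(EA) − β2(SA).

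The time term cancels, so the result does not depend on j. It holds whether time is a factor or a number. Adding baseline does not change it; only a time × treatment term does.

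**2. What that one number is.** With complete, balanced visits and exchangeable within-patient correlation, the treatment coefficient equals the simple mean of the four visit-specific differences. With missing visits it is a weighted mean.

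**3. Distance from week 8.** The documents give no NRS effects, so the profiles below are assumptions (size of benefit at weeks 4, 8, 16, 26). The two rising profiles are the same four values in ascending order.

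| Assumed profile | Mean | Week 8 | Model relative to week 8 |
|---|---|---|---|
| Constant | same value | same value | no gap |
| 0.5, 1.0, 0.7, 0.3 | 2.5/4 = 0.625 | 1.0 | 0.375/1.0 = 37.5% too small |
| 0.8, 1.2, 0.6, 0.2 | 2.8/4 = 0.70 | 1.2 | 0.50/1.2 = 41.7% too small |
| 0.3, 0.5, 0.7, 1.0 | 2.5/4 = 0.625 | 0.5 | 0.125/0.5 = 25% too large |
| 0.2, 0.6, 0.8, 1.2 | 2.8/4 = 0.70 | 0.6 | 0.10/0.6 = 16.7% too large |

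**4. Simulation check.** Assumptions: 160 per arm, 40 replicates, subject SD 1.3, residual SD 1.3, baseline measurement SD 1.2, categorical time, true EA−SA NRS differences −0.6, −1.2, −0.6 and 0.0 (mean −0.60).

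| Model | EA−SA estimate |
|---|---|
| As printed | −0.61 at every week (SE 0.162) |
| Baseline added, no interaction | −0.59 at every week (SE 0.123) |
| Baseline and time × treatment | −0.58, −1.20, −0.59, 0.00 |

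The interaction recovers the weekly values. Baseline alone improves precision and leaves the estimate constant over weeks.

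**5. What a weekly contrast costs in precision.** Under the same assumptions, the between-patient variance after adjusting for baseline is 1.69 × 1.44/(1.69 + 1.44) = 0.778.

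- Follow-up average: SE = √[2/160 × (0.778 + 1.69/4)] = 0.122, in line with the simulated 0.123.
- Single week: SE = √[2/160 × (0.778 + 1.69)] = 0.176.

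The single-week CI is about 0.176/0.122 = 1.4 times as wide.

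**6. The primary analysis is untouched.** For 60% vs. 40%, two-sided alpha 0.025 and power 80%, the pooled formula gives [2.241·√0.5 + 0.842·√0.48]²/0.2² = 117.5. The continuity correction gives 117.5/4 × [1 + √(1 + 4/(117.5 × 0.2))]² = 127.3, so 128 per group. Then 128/0.8 = 160, and 3 × 160 = 480. Both plan figures reproduce, and neither involves the mixed model.

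**The case against.** The strongest reply is that these outcomes only support the conclusion and that the interaction model is already pre-specified, so the dispute is about which of two declared models leads. An average effect over follow-up is a legitimate estimand. Table 2 may also be a generic shell: it has a baseline row of differences that no model of follow-up scores can produce, and its single P value per pair does fit the main-effects model.

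Much of this stands. It limits the severity, and it means the plan as a whole is not unable to produce weekly differences: the second model can do so if time is categorical. What survives is that the model named as main cannot fill the cells, the plan does not say what does, and the P value tests something other than the differences beside it.

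A reader might infer more, which the article does not support:

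- **That the trial's 8-week question is compromised.** The hypotheses concern response rate and are tested by the Z-test.
- **That time is modelled as a straight line.** The same notation gives one coefficient to a three-level treatment and one to nine centers, so β is evidently shorthand for factor effects. The coding of time is simply not stated.
- **That within-patient correlation is forced to be constant.** R_i is left unrestricted.
- **That baseline adjustment will be dropped and precision lost.** The text says baseline is a covariate, so this is a mismatch between words and equation. It plays no part in the loss of weekly differences.

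**Conclusion.** The point holds for NRS, the three WOMAC subscales and the two SF-12 scores. That the main model's treatment difference is the same at every week is exact algebra. That Table 2 asks for weekly differences, and that baseline is named in the text but missing from both equations, can be read directly from the article.

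The size of the consequence is not fixed by the documents. The 37–42% understatement arises from assumed profiles chosen to peak at week 8. A constant effect gives no gap, and a rising effect reverses the sign. It should not be quoted as an expected bias.

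This should be fixed, but it does not threaten the trial's main conclusion. It affects how the supporting results are estimated and read.

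**What to change.** - Make the main model: baseline value + categorical time + treatment + time × treatment.
- Add the baseline term to both printed equations, so that they agree with the text.
- State that Table 2's follow-up differences, 95% CIs and P values come from this model's weekly contrasts, one P value per weekly contrast, and name week 8 as the key contrast.
- Keep the no-interaction model as a supplementary analysis, labelled as an average over follow-up.

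Center in the main model and an unstructured within-patient covariance over the four visits are reasonable options, but the defect can be cured without them.

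The cost is SAP wording and a few lines of PROC MIXED, with no new data and no change to the sample size. The one statistical price is a wider CI for a single week than for the average.

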### Outcomes

#### Primary outcome

The primary outcome is the response rate [20], which is the proportion of patients who achieve the minimal clinically important improvement in pain and function at 8 weeks post-randomization. The average pain over the previous week will be assessed using an 11-point numerical rating scale (NRS) [21] with scores ranging from 0 to 10. The minimal clinically important improvement in pain is defined as 2 points in the NRS [11, 22]. The average function over the previous week is measured using the Western Ontario and McMaster Universities Osteoarthritis Index (WOMAC) function subscale [23] with scores ranging from 0 to 68. The minimal clinically important improvement in function is defined as 6 points in the WOMAC function subscale [11, 22]. The criteria for a participant to be a responder are presented in Fig. 1. The response rate is also measured at weeks 4, 16, and 26 after randomization.

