#### Secondary outcomes

The secondary outcomes are:Numerical rating scale [21]: an 11-point patient-reported outcome measure (PROM) with scores ranging from 0 (no pain) to 10 (worst pain)WOMAC [23] pain subscale: a 5-item PROM with total scores ranging from 0 to 20; higher scores indicate worse painWOMAC [23] function subscale: a 17-item PROM with total scores ranging from 0 to 68; lower scores indicate better physical functionWOMAC [23] stiffness subscale: a 2-item PROM with total scores ranging from 0 to 8; higher scores indicate more stiffnessPatient global assessment [24]: a 5-point Likert scale12-item Short Form Health Survey (SF-12) [25] physical dimension: total scores range from 0 to 100; lower scores indicate a worse quality of lifeSF-12 [25] mental dimension: total scores range from 0 to 100; higher scores indicate a better quality of life

For the patient global assessment, participants are asked how their knee symptoms were during the past week. Answers can include “extremely improved,” “slightly improved,” “not changed,” “slightly aggravated,” and “extremely aggravated.”

The NRS, WOMAC, patient global assessment, and SF-12 are measured at 4, 8, 16, and 26 weeks after randomization. The blinding assessment is measured at 4 and 8 weeks after randomization. The credibility and expectancy of participants are measured 5 min after the first acupuncture session [26]. The use of rescue medicine is also recorded throughout the trial.

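### The normality-triggered transformation of secondary scores tests the wrong quantity, would be triggered for the short scales under a usual formal test, and moves the model off Table 2's point scale

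*SAP article*

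**What the plan says.** The section on analysis of secondary outcomes sets up a repeated-measures mixed model for the NRS, with a normal subject effect and a normal error term. It then extends the model: "The same approach will be used to analyze the pain, function, and stiffness WOMAC subscales, and SF-12". The next sentence is the one at issue: "If normality is violated in the continuous variables, a transformation will be performed before the comparison".

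The scales are described under secondary outcomes. The NRS has 11 points, from 0 to 10. WOMAC pain is "a 5-item PROM with total scores ranging from 0 to 20", WOMAC function "a 17-item PROM with total scores ranging from 0 to 68" and WOMAC stiffness "a 2-item PROM with total scores ranging from 0 to 8". Each SF-12 dimension runs from 0 to 100.

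Table 2 fixes the display. Each of these outcomes is headed as mean and SD (for example "Numerical Rating Scale, mean (SD)"), with pairwise columns for a difference, its 95% CI and a P value. The table makes no provision for a transformed scale. The general analysis principles make the secondary outcomes supportive of the primary one.

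**The concern.** There are three problems with the rule as stated.

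- **Wrong target.** It looks at the variables. The model needs approximate normality of the random effects and errors, given treatment, time and baseline. Raw scores can fail a normality test while the model is adequate.
- **Data-driven step.** Whether to transform, and on this wording which transformation to use, is settled after the scores are seen. The article says that it exists to prevent data-driven analysis.
- **Change of scale.** After a square-root or log-type transformation, the treatment coefficient is no longer a difference in mean points. Table 2 has raw-looking means and SDs beside a difference, a CI and a P value. If the P value comes from the transformed model while the difference and CI stay in points, the two test different quantities and can contradict each other in the same row.

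At stake are the readability and internal consistency of the pain, function, stiffness and quality-of-life results.

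**Working it through.** **Sample size per arm.** The only computed figure in the plan is the sample size, and it fixes the numbers used below. For 60% against 40%, two-sided alpha 0.025 and power 80%, the pooled formula is

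n = [2.2414·√(2·0.5·0.5) + 0.8416·√(0.6·0.4 + 0.4·0.6)]² / 0.2² = 117.5, so 118 per group.

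With continuity correction,

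(117.5/4)·[1 + √(1 + 4/(117.5·0.2))]² = 127.3, so 128 per group, as stated.

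Then 128/(1 − 0.20) = 160 per arm and 3 × 160 = 480. The plan's figure reproduces, and this point does not affect it.

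**Assumptions for the rest.** The article names no normality test and no transformation, and gives no means or SDs for these scores. The checks therefore assume Shapiro-Wilk at 0.05, rounded normal scores clipped to each scale's range, and a square root or log(x+1) as the transformation.

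**How often the rule is triggered** (500 simulated samples per cell; n=160 is one arm at one visit, n=480 is all arms):

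| Scale | Assumed mean (SD) | n=160 | n=480 |
|---|---|---|---|
| NRS 0–10 | 3, 4 or 5 (2) | 100% | 100% |
| WOMAC stiffness 0–8 | 2 or 4 (1.7) | 100% | 100% |
| WOMAC pain 0–20 | 5 (3.5) | 100% | 100% |
| WOMAC pain 0–20 | 8 (3.5) | 40% | 100% |
| WOMAC function 0–68 | 18 (12) | 97% | 100% |
| WOMAC function 0–68 | 25 (12) | 12% | 85% |
| WOMAC function 0–68 | 34 (11) | 5% | 7% |
| SF-12 0–100 | 40 or 50 (9) | 6% | 11–12% |

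The NRS is rejected even at mean 5, in the middle of its range, where there is little skew. The test is reacting to the small number of distinct values. A one-to-one transformation of an 11-level score still has 11 levels, so it cannot cure what triggered it.

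**Disagreement between scales.** Two-sample t-tests at 160 per arm, 4,000 runs, gave this share of trials in which the raw and transformed tests fall on opposite sides of 0.05:

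| Scenario | Square root | log(x+1) |
|---|---|---|
| NRS, mean 3.5, SD 2, difference 0.5 | 10.2% | 10.4% |
| NRS, no difference | 2.4% | 2.5% |
| WOMAC function, mean 20, SD 12, difference 3.3 | 9.7% | 17.1% |
| WOMAC function, no difference | 2.4% | 4.5% |

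The check was also made with ANCOVA on each patient's visit average, which with complete data is equivalent to the planned random-intercept test of treatment. Disagreement was 3–4% with no effect and 6–13% with a true effect. A further ANCOVA check under other assumed values gave about 3–7%.

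**What the raw scale costs.** Type I error of the raw t-test at 160 per arm (40,000 runs) was 0.0505 for the NRS, 0.0504 for stiffness and 0.0496 for a score with 40% of values at zero. With the ANCOVA (8,000 runs per scenario) it was 0.047–0.052 across the scales. ANCOVA power for the NRS was 0.81 raw against 0.79 for both transformations. For WOMAC function it was 0.86 raw, 0.84 square root and 0.77 log(x+1).

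**The case against.** The strongest reply is that this is one short sentence in a condensed article about supportive outcomes. The approved SAP version 1.0 is not shown and may name the diagnostic, the transformation and the reporting scale. The same section states normality for the subject effect and the error, so the reference to variables may be loose wording. That stands as a caution, and the point therefore does not rest on missing detail. It rests on the rule the article does state, which directs a data-dependent change of scale where a fixed raw-scale model would serve better.

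Several stronger readings are tempting but not supported:

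- *The rule is triggered for every outcome.* It is not. For SF-12 the rate is low under near-normal scores, and for WOMAC function it depends almost entirely on where the mean falls. If normality were judged by eye, no rate can be given.
- *The P values will contradict the differences.* They can. The article does not say that P values come from one scale and differences from another. Table 2 is an empty shell with no units on its difference columns. Back-transformed means can be differenced with delta-method or bootstrap CIs. In most simulated trials both scales agreed on significance.
- *The 2-point NRS and 6-point WOMAC function thresholds are undermined.* The article's statement that "The minimal clinically important improvement in pain is defined as 2 points in the NRS", like its 6-point counterpart, serves to classify individual patients as responders. The plan does not use either value to judge differences in group means.
- *A log fails at a score of 0.* The plan names no log, so this is no fault of it.

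It is also fair to say that the full repeated-measures model with dropout was not simulated. The ANCOVA on visit averages matches it only for complete data.

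**Conclusion.** The point holds in a limited form. The rule checks raw scores although the model's assumption concerns random effects and errors. Under a usual formal test it would take the NRS and WOMAC stiffness off the point scale, and in most settings WOMAC pain as well. For WOMAC function and SF-12 the outcome is open until the data are seen.

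The possible inconsistency between a P value and a point-scale CI ranged from a few percent to about 17% of simulated trials. Raw-scale analysis at about 160 per arm showed no loss of type I error control and no loss of power in the scenarios tried. These figures depend on the assumed means, SDs, test and transformations, none of which the article supplies.

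A reader might infer that the trial's main conclusion is exposed. It is not: the primary outcome is a responder proportion compared by a Z-test, which this sentence does not affect, and the article bases its conclusions on that outcome.

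**What to change.** Delete the sentence and put in its place that:

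1. The NRS, the three WOMAC subscales and both SF-12 dimensions are analysed on their original point scales with the pre-specified mixed model, whatever a normality test shows.
2. Model residuals are inspected, not the raw scores.
3. Bootstrap or sandwich CIs for the same model are reported as a sensitivity analysis only.
4. Every P value in Table 2 comes from the same model and scale as the difference and CI beside it.

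The cost is a few lines of wording and, for sandwich standard errors, the EMPIRICAL option in PROC MIXED. The downside is that sandwich standard errors need care when visits are missing, and the plan allows for 20% loss to follow-up. For that reason they belong in the sensitivity analysis and not in the main one.
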